### Analysis

Appropriate longitudinal analysis will be conducted using ANOVA and multilevel modelling (via R software or SPSS v26) to assess differences in self-reported outcomes between the telehealth intervention group and the comparator group. Key outcomes include adherence, digital health literacy, satisfaction with care, mental health indicators, and service use for primary and secondary care. Additionally, subgroup analysis will explore survey responses based on sociodemographic factors such as place, deprivation, ethnicity, age, and sex.

**Work package 3:**  *To interview patients and staff and understand the barriers and enablers of effective service delivery care*

### Methods

Remote (Microsoft Teams or telephone) semi-structured one-to-one interviews will be conducted with patients receiving the MCTS and staff delivering the MCTS or who are involved in the implementation of the MCTS. Informed by the Consolidated Implementation Framework for Research (Damschroder et al., 2009), two topic guides have been devised (one for patients, one for staff) in collaboration with Patient and Public Involvement (PPI) study team members ([name], [name]) and staff delivering the MCTS. Staff interviews will focus on participants’ professional roles, challenges, benefits, and suggestions for the telehealth system, as well as equity considerations and potential expansions to mental health services. Patient interviews will gather information about their health conditions, experiences with the MCTS, equity issues, and views on expanding the service to mental health care.

A total of 30 interviews, with *n* = 15 patients and *n* = 15 staff, will be held. Table 3 summarises the inclusion and exclusion criteria for each study population, Purposive sampling will be employed to increase the representativeness of our sample (Palinkas et al., 2015). We aim to interview patients with a range of different health conditions, patient-level socio-demographic characteristics (including deprivation and ethnicity), and experiences of accessing different monitoring levels (full, stepped down or light touch, and self-monitoring*)*. Moreover, we aim to interview staff with different roles and responsibilities who are involved in the implementation or delivery of the MCTS.

**Table 3 TB3:** The inclusion and exclusion criteria for each study population, and variables included in the sampling matrices.

Patients		Staffs	
Inclusion	Exclusion	Inclusion	Exclusion
MCTS patients diagnosed with HF, COPD and/or diabetes; included within the CMI system; consenting to participant	Not diagnosed with HF, COPD and/or diabetes; not listed on the CMI system; lack of mental capacity to consent as identified by MC staff, not consenting to participate	Staff who are involved in the implementation or delivery of the MCTS with or without patient contact, including nurses, healthcare assistants and administrative staff	Those who are not involved in the implementation or delivery of MCTS Those not consenting to participate.

**Abbreviations:** CMI—Count Me In; HF—Heart Failure; COPD—Chronic Obstructive Pulmonary Disease; MC—Mersey Care.

Patient participants will be recruited using Mersey Care’s ‘Count me in’ CMI system (NHS Mersey Care, 2025). The research opportunity and participant information sheet will be shared with potential patient participants according to their preferred method of contact. Staff participants will be recruited by email, through a study team member ([name]), who is involved in the delivery of the MCTS. Informed consent (verbal or digital) will be obtained and recorded prior to interviewing. Interviews will be audio-recorded and transcribed verbatim.

### Analysis

Anonymised transcripts will be imported into NVivo-QSR 12 for analysis (Dhakal, 2022). Analysis will be informed by thematic approaches (Braun and Clarke, 2006) and the Consolidated Framework for Implementation Research (Damschroder et al., 2009). Survey responses from WP2 will be used to triangulate our qualitative analysis thereby increasing our understanding of patient experiences. Where participants have consented, member checking approaches will be employed to validate the main themes generated. PPI study team members ([name], [name]) will be involved in the analysis and advise on the interpretation of the findings.

**Work package 4:**  *To find out whether Mersey Care Telehealth Service is cost-effective*

### Methods

We will conduct a cost-utility analysis using quality of life data (RQ2), service costs, and information relating to healthcare resource use (RQ1). We will develop an economic model that considers health outcomes, health and social care service use (primary, secondary care, social care and care/nursing home admission), informal care costs and cost of resources, and estimates the incremental cost effectiveness ratio expressed as cost per quality adjusted life year in line with NICE guidance. The healthcare resource use will be measured from RQ1 and costs for the intervention and control group will be attached using NHS reference costs and Personal Social Services Research Unit reference costs for health and social care, possibly augmented with any local costs where necessary.

### Data and measures

Metrics for cost utility analysis will include quality of life measures (EQ-5D-3L from telehealth and WP2 survey data), service costs from Mersey Care, and health and social care use metrics. Additional measures may be taken as needed for model development. There is no applicable sample size or specific participant recruitment for this research question, as it relies on data collected for other research questions.

### Analysis

The model will be constructed using a 6 months-time horizon (within trial economic evaluation) and a 10-year time horizon using longer term follow up data for the programme and control groups. If there is not adequate person-years of follow up, then the data can be augmented with modelled estimates from other sources, such as English Longitudinal Study of Ageing and Health Survey for England. EQ-5D-3L score trajectories for control group will be estimated using Health Survey for England 2014 data and use Manca’s methods to control for differences in baseline utility (Manca et al., 2005). Health inequalities will be taken into consideration, and the model will account for outcomes disaggregated by IMD quintile. This may include carrying out distributional cost effectiveness analysis to look at cost effectiveness by IMD quintile.

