### Methods

Using a prospective study of 2,000 patients accessing MCTS and a comparison group of 2,000 who declined the service. We will gather survey data from telehealth patients on various health metrics, at 1-and 12-weeks post-enrolment, and we will contact patients, monthly, who have recently declined to use the service and collect baseline data and 12-week follow-up data for comparison.

The survey will include measures of health-related quality of life (EQ-5D-3L); Patient Health Questionnaire-9 (PHQ-9); Generalised Anxiety Disorder Questionnaire (GAD-7); Digital Health Literacy Scale (Nelson et al., 2022), and using MCTS standard survey questions, collect information on telehealth care support, patient satisfaction and evaluations on care quality and communication with healthcare professionals. Demographic information for MC telehealth patients is routinely collected. Thus, the survey for the comparator group will gather the following demographic information: health conditions (COPD, HF, and diabetes), age, sex, ethnicity, postcode, English language fluency, number of people living in the household, and reasons for declining the telehealth service for the comparison group to analyse deprivation indices. Our survey questions were based on those used by the Office for National Statistics (Office for National Statistics, 2023).

Our intervention group survey sample size is based on the size of the population of interest (people using the telehealth service), the level of confidence, and the degree of margin of (random) error. Our population is the approximately 22,000 patients who have used the MCTS. With a confidence level of 95%, a sample of 2,000 telehealth patients would provide a margin of error between 2% and 3% in how the responses would represent those of the total population. We feel that this is an acceptable margin of error. For a margin of error of 3% we would require 1,018 responses and so this allows for sufficient loss to follow-up from the target 2,000 participants. As such we require a similar size in the comparator group.

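### WP4 states without restriction that control-group EQ-5D-3L comes from a 2014 national survey, in conflict with its own commitment to WP2 data, and its 6-month within-study horizon runs about 14 weeks past the last scheduled survey

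*Protocol article*

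**What the plan says.** The protocol article describes the utility data for the economic evaluation in four places.

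- **WP2, Methods.** The survey includes EQ-5D-3L. Telehealth users (target 2,000) are surveyed 1 and 12 weeks after enrolment. For a comparison group of 2,000 who declined the service, the team will "collect baseline data and 12-week follow-up data for comparison". No later survey is described.
- **WP4, Methods.** The cost-utility analysis takes its quality-of-life data from RQ2, that is, from WP2.
- **WP4, Data and measures.** The utility source is given as "EQ-5D-3L from telehealth and WP2 survey data". No external survey is named.
- **WP4, Analysis.** "The model will be constructed using a 6 months-time horizon (within trial economic evaluation) and a 10-year time horizon". The text then says: "If there is not adequate person-years of follow up, then the data can be augmented with modelled estimates from other sources". The next sentence reads "EQ-5D-3L score trajectories for control group will be estimated using Health Survey for England 2014 data", and adds that an established regression method will be used "to control for differences in baseline utility".

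**The concern.** The sentence on augmenting the data makes external sources conditional on short follow-up. The sentence on control-group EQ-5D-3L carries no such condition and is not tied to the 10-year horizon. An analyst who follows it literally would use the 2014 survey for the control group in the within-study analysis too, even though the study plans to collect the same instrument from its own comparator group.

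The incremental QALY would then be utilities measured in users minus a modelled path from different people in a different period. Any difference in population, period or selection between the two sources would be counted as part of the service effect. The cost per QALY, and the results by IMD quintile, rest on that increment.

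The second problem stands whichever way the survey sentence is read. The within-study horizon is 6 months, but the last scheduled EQ-5D-3L is at week 12, and the article does not say how utilities are carried from there to 6 months.

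**Working it through.** **Side check on the plan's own figure.** WP4 states no sample size. WP2, which supplies the EQ-5D-3L, states 1,018 responses for a 3% margin of error in a population of 22,000.

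- n0 = 1.96² × 0.25 / 0.03² = 1,067.1
- n = 1,067.1 / (1 + 1,066.1 / 22,000) = 1,017.8, rounded up to 1,018

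The figure reproduces and is not in dispute.

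**Coverage of the 6-month horizon.** Inputs: horizon 6 months (WP4, Analysis); last survey at week 12 in both groups and first survey in users at week 1 (WP2, Methods).

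- 6 months = 365.25 / 2 / 7 = 26.09 weeks
- Covered up to the last survey: 12 / 26.09 = 46%
- Between the users' two surveys: 11 / 26.09 = 42%
- After the last scheduled survey: 14.09 / 26.09 = 54%

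**Effect of a mismatch between the external path and the true control path.** The protocol gives no utility values, so the mismatch d is assumed and a range is shown. Two cases bracket what baseline adjustment could do.

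- Constant level difference over 6 months: shift = d × 0.5 year
- Baseline level fully removed, with linear drift from 0 to d at 6 months: shift = d × 0.5 / 2

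| Assumed d | Constant level (QALY) | Drift only (QALY) |
|---|---|---|
| 0.01 | 0.005 | 0.0025 |
| 0.02 | 0.010 | 0.005 |
| 0.05 | 0.025 | 0.0125 |
| 0.10 | 0.050 | 0.025 |

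Baseline adjustment at its best halves the shift in this set-up. It does not remove it, because it acts on the starting level and not on the slope.

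**Effect of the unscheduled 14 weeks.** Assume a true utility gain of 0.05 at week 12, reached linearly. Twelve weeks is 84 / 365.25 = 0.230 year, and the remainder to 6 months is 0.270 year.

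- Gain lost after week 12: 0.05 × 0.230 / 2 = 0.006 QALY
- Gain waning linearly to zero by 6 months: 0.00575 + 0.05 × 0.270 / 2 = 0.0125 QALY
- Gain held to 6 months: 0.00575 + 0.05 × 0.270 = 0.019 QALY

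The same 12-week data give roughly a 3.3-fold range in the 6-month QALY gain (0.01925 / 0.00575), set by the extrapolation rule alone.

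**The case against.** The strongest reply is that the survey sentence describes extrapolation only. It directly follows the sentence on augmenting short follow-up, which names the same survey series, and both come after the 10-year horizon. The other two WP4 sections commit to WP2 data. The baseline-utility adjustment makes most sense if individual WP2 utilities enter the comparison. This reading is plausible, and a reader should not infer that the plan discards the decliners' EQ-5D-3L, because nowhere does it say so. What remains is that the sentence is unrestricted as written and conflicts with the sections before it.

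Three other stronger readings are not supported.

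- **That no EQ-5D exists after week 12 in either group.** The article says only that none is scheduled in the WP2 survey. The service collects quality of life through its own questionnaires, WP4 lists telehealth data separately from the WP2 survey, and it leaves room for additional measures. Later user data are possible, though none is stated. For the comparator group the two survey times are explicit.
- **That the increment would count recovery from an acute episode as benefit.** Entry is by predicted risk, GP referral or step-down. Nothing says that enrolment follows an acute event, and the direction of any bias cannot be read from the documents.
- **That a single constant mismatch, such as 0.05, sizes the error.** It would be an assumption, and the constant-level case is the larger of the two because some baseline adjustment is planned.

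It is also fair to say that WP2 data are no perfect remedy. WP2 itself grants that decliners are a selected comparator. Users are first surveyed a week after enrolment, so neither source gives them a pre-treatment utility. A 12-week window is shorter than the usual first monitoring period of up to 5 months. These points limit the fix but do not favour the external 2014 path for the within-study comparison.

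**Conclusion.** The point holds as a conflict in the stated text plus a gap in the horizon. WP4, Analysis, assigns control-group EQ-5D-3L to an external 2014 survey without restriction, while the rest of WP4 relies on WP2, which plans to measure EQ-5D-3L in the comparator group. Followed literally, the within-study QALY difference would compare measured with modelled utilities, and the named adjustment could not correct a difference in trajectory.

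The possible shift is 0.005 to 0.05 QALY (constant level) or 0.0025 to 0.025 QALY (drift only) for assumed mismatches of 0.01 to 0.10. These are illustrations. The effect on the cost per QALY cannot be sized, because the article gives neither utilities nor costs. The finding that 54% of the 6-month horizon lies beyond the last scheduled survey needs no such assumption.

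**What to change.** Reconcile the three WP4 sections as follows.

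1. Use WP2 EQ-5D-3L from both groups for the within-study analysis, with the weighting, matching or covariate adjustment already planned in WP2 and adjustment for utility at the first survey. State that the users' first survey is at week 1 after enrolment, and that decliners remain a selected comparator after adjustment.
2. Report the QALY difference over the observed 12 weeks. Present the 6-month figure as an extrapolation with named scenarios: gain lost, waning or held after week 12.
3. Confine the Health Survey for England 2014 to the long-term model and a scenario analysis, and say so in the sentence that names it.

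This needs changes of wording and some additional scenario runs, but no new data collection. The cost is that the within-study estimate may be less precise, and that its observed window is shorter than the usual monitoring period of up to 5 months, so some costs and effects of the service fall in the extrapolated part.

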## Patient and public involvement and engagement

Two public advisors ([name], [name]) are part of the research team contributed to the study design, reviewed study documents, and will be involved in the analysis, interpretation, and dissemination of our findings. [name] & [name] have lived experience of multiple long-term conditions, including mental health issues. They have extensive experience of being involved with research teams and working to embed a health equity approach to research via their work in NIHR Applied Research Collaboration North West Coast.

We will work together to complete the NIHR Health Inequalities Assessment Toolkit (rebranded into For Equity) (FOR-EQUITY, 2025) to ensure equity in telehealth access is maintained. It will be revisited regularly to ensure that issues of equity will be kept in focus throughout life of the project. To ensure that the project is inclusive and addresses the needs of people with mental health problems, we will work with the PPI team of the recently established Mental Health for Innovation (M-RIC) research facility (Mersey Care NHS Foundation Trust, 2025b).

Public advisors will be paid in accordance with the Involve guidelines. Training will be provided either via NIHR ARC NWC or on a one-to-one basis from research members of the team. PPI activities will be recorded and reported at the end of the study; the impact will be assessed using a bespoke, co-produced impact log and PPI reporting will be guided by the Guidance for Reporting Involvement of Patients and the Public (GRIPP2) tool (Staniszewska et al., 2017).

## Discussion

This protocol describes a multi-method study seeking to evaluate the effectiveness of the MCTS by assessing unplanned healthcare utilisation, patient-reported outcomes, implementation barriers and enablers, and cost-effectiveness. Telehealth has emerged as a key approach to support the transformation of the health system, especially in the NHS, where growing health disparities, multimorbidity, and service pressures have increased demand for digitally enabled care. To ensure that the implementation of telehealth is clinically effective, financially sustainable, equitable, and in line with the needs of patients and healthcare professionals, the study’s findings will support well-informed decision-making at the local, regional, and national levels (Department of Health & Social Care, 2022; NHS England, 2019a; NHS England, 2025b; NHS England, 2024a). This study examines health inequalities throughout. In WP1, we plan to explore deprivation, geographic location (place), ethnicity, age, sex, and service type as part of subgroup analyses. We will take a data-driven approach to define sub-groups to ensure that there is a sufficient number of participants within sub-categories to produce robust results. We will re-run the analyses within each sub-group to explore the impact of the telehealth service in the different groups. Within WP2, data permitting, we also plan to explore survey responses by deprivation, ethnicity, age, and sex. For WP3, we endeavour to employ a purposive sampling approach to interview a range of telehealth patients and staff. Furthermore, for WP4, we will consider outcomes across socioeconomic groups, stratified by IMD quintile.

### Limitations of the study

Several limitations are anticipated. First, the use of observational data introduces the potential for residual confounding, despite the use of propensity-score matching and multivariable modelling to mitigate these risks. Secondly, as this is a single-site study (Mersey Care NHS Foundation Trust), the findings may have limited generalisability. Third, routine clinical and administrative datasets may contain missing or incomplete data, particularly regarding socio-demographic variables or patient-reported outcomes. Qualitative components aim to mitigate this by including a diverse sample; however, some underrepresented voices may remain difficult to reach. The qualitative interviews may be influenced by selection bias, as participants who engage may have more positive experiences. Furthermore, the economic evaluation may be influenced by uncertainties in costing remote monitoring infrastructure, although sensitivity analyses will help to address this.

## Ethical and regulatory considerations

### Ethics approval

Ethical approval was obtained from the Health Research Authority and Health and Care Research Wales Ethics Committee (Ref: 25/NW/0268).

### Assessment and management of risk

A study risk assessment will be completed as part of the sponsor review process. It is important that people accessing the MCTS who are living with HF, COPD and/or diabetes can take part in our interview process, so we have a better understanding of their experiences of the service. However, although it is not anticipated that any interview questions will cause upset, it is possible that discussing their experiences might cause some distress, therefore we will ensure an ethically approved distress process is in place that has been co-produced with members of the Patient and Public Involvement and Engagement team.

### Peer review

To secure funding for this research programme, the application process involved two stages of scientific review conducted by the NIHR RfPB. In addition, we have an external peer review.

### Data protection/confidentiality

Cheshire and Merseyside have a Secure Data Environment that houses patient-level linked data for planning, population health, and research. Managed by Cheshire and Merseyside Integrated Care Board and hosted by the Data Service for Commissioners Regional Office through Arden & GEM Commissioning Support Unit, the SDE serves various stakeholders, including commissioners, local authorities, providers, and researchers. Built on Azure Cloud, the SDE provisions data on a project-by-project basis using an ‘Airlock’ system, ensuring all analysis occurs within the environment, and data cannot leave without approval under strict minimisation criteria.

The SDE integrates data from three main sources: National Commissioning Datasets from NHS England, local provider data flows, and the Cheshire and Merseyside Shared Care Record managed by Graphnet. All data within the environment is de-identified, removing direct identifiers while maintaining pseudonymised records for research use. Data access is granted on a project basis through the Cheshire and Merseyside Data Access and Asset Group, which includes representatives from data controllers, processors, a Data Protection Officer, Caldicott Guardian, and public members. Applicants must submit a Data Access Request Form detailing project scope, legal basis, datasets, data flow, and governance measures. Individuals retain the right to opt out of data sharing through nationally defined processes.

Participant confidentiality will be maintained in accordance with the Data Protection Act 2018, UK General Data Protection Regulation, and applicable data protection legislation. Mersey Care NHS Trust is the data controller. Researchers at the University of Liverpool will collect participant names and informed consent records for the qualitative studies involving MC telehealth staff (including nurses, healthcare assistants, and administrative staff), patients receiving the telehealth service, and patients who declined the service. All data will be managed in accordance with NHS Research Ethics Committee–approved procedures.

